#### Organisational system and process measures

A number of service variables will be measured to examine the relationship between the organisational change intervention and different organisational structures. Structural variables, which will be collected from the head of each treatment service prior to randomisation using an online survey, will include the number of new patients each year, number of full-time and part-time staff, type of treatment provision (e.g. opiate, alcohol or combined) and governmental or non-governmental organisation. At 6-week follow-up, the clients will be asked to indicate which components of the smoking cessation intervention they were offered and/or received.

### Sample size

Within each participating cluster, recruitment will occur over a continuous 6-month period, with the aim of recruiting 35 eligible clients per week (approaching 60 patients with 60 % consent [44, 45]) and giving a sample size at baseline of approximately 450 per group. Although strategies will be employed to reduce attrition and maximise retention, based on previous research [46, 47] 40 % are expected to be lost to follow-up at 6 weeks, thereby providing a sample of 270 participants per experimental arm (an average of 16–17 per treatment centre). Assuming a 5 % significance level, 80 % power, 5 % smoking cessation in the control group for 7-day-point prevalence, a design effect of 1.4 due to correlation of observations within treatment services (an intra-class correlation coefficient of approximately 0.025), and a 10 % allowance for unequal sized clusters, this sample will allow detection of a 9 % difference in the 7-day-point prevalence of abstinence between groups at 6 weeks. For the secondary outcomes, the study will have 80 % power, with a 5 % significance level to detect difference between groups in the 6 week self-reported 7-day-point prevalence of abstinence, use of cessation aids of approximately 9 %, and approximately one quarter of a standard deviation in nicotine dependence and self-reported number of quit attempts. We anticipate a 6-month attrition of 50 %, with detectable differences of 10–11 % for binary outcomes and one third of a standard deviation for continuous outcomes.

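### The 6-week detectable effect of one quarter SD is optimistic: the stated inputs give about 0.30 SD, and about 65% power at 0.25 SD

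*Protocol article*

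**What the plan says.** All the planning figures are in the Sample size section of the protocol article.

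- **Numbers.** The baseline target is given as "giving a sample size at baseline of approximately 450 per group". The attrition assumption is "40 % are expected to be lost to follow-up at 6 weeks". The number of completers that follows is stated in these words: "thereby providing a sample of 270 participants per experimental arm (an average of 16–17 per treatment centre").
- **Clustering.** The design effect is 1.4, from an intra-class correlation of about 0.025, with a further 10% for unequal cluster sizes. These appear in the sentence on the primary outcome, which gives a detectable difference of 9% from 5% control cessation.
- **Secondary outcomes at 6 weeks.** "For the secondary outcomes, the study will have 80 % power" at the 5% level. The detectable effects include "use of cessation aids of approximately 9" per cent, and "approximately one quarter of a standard deviation in nicotine dependence and self-reported number of quit attempts".
- **6 months.** With 50% attrition, the detectable effects are 10–11% for binary outcomes and "one third of a standard deviation for continuous outcomes".

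The Data analysis section uses mixed models to allow for correlation within treatment centres, with the stratification factors as the named covariates. The heaviness of smoking index is analysed by linear regression and quit attempts by negative binomial regression.

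**The concern.** The two standard-deviation figures do not sit together. At constant inflation, the detectable effect scales with one over the square root of the sample size. Going from 270 to 225 per arm should therefore raise it by a factor of √(270/225) = 1.095, but the stated move from one quarter to one third is a factor of 1.333. Smaller clusters at 6 months would lower the design effect and reduce the expected factor further.

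The issue is whether the claimed 80% power exists for two named secondary outcomes. If it does not, a null result on nicotine dependence or quit attempts could be taken as stronger evidence against an effect of a quarter SD than the trial can supply.

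**Working it through.** **Inputs (Sample size section).** Completers per arm: 450 × 0.6 = 270 at 6 weeks and 450 × 0.5 = 225 at 6 months. Design effect 1.4, which agrees with 1 + (17 − 1) × 0.025 = 1.40. Unequal-cluster allowance 10%, so total inflation is 1.4 × 1.1 = 1.54. Power 80%, significance 5%. Two-sided testing is assumed, since the article does not say, so z-values are 1.960 + 0.8416 = 2.8016.

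**Formulas.** Effective size n_eff = n / inflation. For means, detectable effect in SD units = 2.8016 × √(2/n_eff), and power at effect d = Φ(d/√(2/n_eff) − 1.96). For proportions, the pooled-variance two-sample formula is solved for the difference.

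**Step 1: the plan's other figures reproduce with the full inflation.**
- Primary outcome: n_eff = 270/1.54 = 175.3. From 5% control, the detectable difference is 8.7 points (9.4 with continuity correction), against the stated 9. With no inflation it would be 6.7.
- 6-month continuous: n_eff = 225/1.54 = 146.1, giving 2.8016 × √(2/146.1) = 0.328 SD, against the stated one third. With no inflation it would be 0.264 SD.
- 6-month binary from 5%: 9.7 points (10.6 with continuity correction), against the stated 10–11.

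**Step 2: the 6-week continuous figure, 270 per arm.**

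| Inflation | n_eff | Detectable effect (SD) | Power at 0.25 SD |
|---|---|---|---|
| none | 270.0 | 0.241 | 83% |
| 1.1 (allowance only) | 245.5 | 0.253 | 79% |
| 1.4 (design effect only) | 192.9 | 0.285 | 69% |
| 1.54 (both) | 175.3 | 0.299 | 65% |

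The last row in full: 2.8016 × √(2/175.3) = 0.299, and Φ(0.25/0.1068 − 1.96) = Φ(0.381) = 0.648. The stated one quarter lies between the two rows that lack the 1.4.

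**Step 3: cross-checks.** Working back from one third SD at 6 months, 0.3333/1.095 = 0.304 SD at 6 weeks. For 80% power at 0.25 SD, 252 independent clients per arm are needed, and 252 × 1.54 = 388 completers per arm, against 270.

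**Step 4: what would recover 0.25 SD.** Baseline adjustment multiplies the detectable effect by √(1 − r²). Setting 0.299 × √(1 − r²) = 0.25 gives r = 0.55 (check: 0.299 × √(1 − 0.3025) = 0.250). With the 1.4 alone, r = 0.48.

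**Step 5: cessation aids (assumed control rates, as the article gives none).** With inflation 1.54, the detectable difference is 8.7 points at 5% control use, 9.2 at 6%, 10.8 at 10%, 13.2 at 20% and 14.4 at 30%.

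**The case against.** The strongest defence is that the figure is loosely rounded and the design effect was not forgotten. Suppose the 10% allowance is applied to cluster size: 1 + (1.1 × 16.4 − 1) × 0.025 = 1.43. Using this inflation at both time points, with continuity correction for the binary outcomes, gives 8.9 points for the primary outcome, 10.1 points at 6 months, 0.288 SD at 6 weeks and 0.315 SD at 6 months. The midpoint between one quarter and one third is 0.292, so a single clustered rule could round to both stated fractions. This stands as an account of how the figure may have arisen. A reader might infer that the design effect was left out, but the article does not show its derivation and does not establish that. The explanation does not rescue the power claim: under this rule, power at 0.25 SD is still about 68%, and the word approximately does not cover such a shortfall.

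The intra-class correlation is also stated only for the primary outcome. Correlations differ between outcomes, and about 0.005 with no unequal-cluster allowance would give 0.250 SD. That stands as a caveat, but no lower value is stated, and the 6-month one third SD fits the stated inflation. One-sided testing with the 1.4 alone would give 0.253 SD at 6 weeks, but only 0.277 SD at 6 months, which does not fit one third.

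A reader might also infer that the 9% for cessation aids is wrong. The document does not support that: it reproduces at 5–6% control use, and larger differences rest on rates the article does not give.

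Finally, these are secondary outcomes, the mixed models will carry clustering into the intervals, and the SD scale is only approximate for a count analysed by negative binomial regression. All of this limits the weight of the point without making the stated power correct.

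**Conclusion.** The stated 80% power for one quarter SD at 6 weeks does not follow from the section's own inputs. The detectable effect is about 0.30 SD (0.285 SD with the design effect alone), and power at 0.25 SD is about 65% (69%), a shortfall of 11 to 15 percentage points. This rests on two-sided 5% testing, on the stated correlation of about 0.025 carrying over to nicotine dependence and quit attempts, and on no covariate gain beyond the named stratification factors. The cause, omission or coarse rounding, remains an inference. The primary outcome's sample size is not affected. For cessation aids the only point is an unstated assumption: 9 points holds if control use is near 5–6%, and would be about 11–14 points at assumed rates of 10–30%.

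**What to change.** In the Sample size section, restate the 6-week detectable effect for nicotine dependence and quit attempts as about 0.30 SD, and say that the primary outcome's intra-class correlation is carried over to them. Alternatively, keep 0.25 SD for nicotine dependence only, provided the analysis adjusts for its baseline value and the assumed baseline-to-follow-up correlation is stated (about 0.55 with the full inflation). If a lower intra-class correlation was intended for these outcomes, state it and its basis.

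For use of cessation aids, state the assumed control rate beside the 9%, and revise the difference if that rate is not near 5–6%.

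The cost is a slightly less favourable figure and one or two added assumptions in the text. No more clients are needed, and the primary sample size does not change.

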### Data analysis

Data will be stored in password-protected files with group code concealed to those who conduct the analysis. A full statistical analysis plan will be developed a priori. Baseline characteristics will be presented for the intervention and control groups. Logistic regression will be used to compare the primary outcome and secondary binary outcomes, linear regression will be used to compare the heaviness of smoking index, and negative binomial regression will be used to compare the number of quit attempts and number of cigarettes smoked between the two groups at each of the two follow-up times. Mixed models will be used to adjust for correlation of outcomes within treatment centres, and models will also include stratification factors (state/territory, service type, smoking policy). Main analyses will involve complete cases, with sensitivity analyses conducted (1) using multiple imputation; and (2) treating missing outcomes as smokers.

The final report will follow the CONSORT 2010 guidelines as well as its extension to cluster trials.

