### Study aims

The primary aim of the Tackling Nicotine Together (TNT) trial is to determine the effectiveness of an organisational change intervention in increasing smoking cessation (7-day-point prevalence of abstinence) amongst clients attending drug and alcohol treatment services. Secondary aims of the trial are to examine the cost-effectiveness of the organisational change intervention compared to usual care and to examine the effectiveness of an organisational change intervention in increasing prolonged smoking abstinence, quit attempts, and the use of cessation aids as well as reducing nicotine dependence amongst clients attending drug and alcohol treatment services. Changes in delivery of smoking cessation care to clients will also be measured.

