#### Baseline characteristics

A number of client sociodemographic, smoking, and clinical characteristics will be obtained, including age, gender, marital status, Aboriginal or Torres Strait Islander status, housing status, income and source of income, education, postcode, smoking profile, and other dependencies (alcohol and other drug use).

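### The models for nicotine dependence and cigarettes smoked do not name the client's baseline value, which gives up precision on two secondary outcomes

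*Protocol article*

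**What the plan says.** Study aims lists among the secondary aims prolonged abstinence, quit attempts and use of cessation aids, "as well as reducing nicotine dependence amongst clients attending drug and alcohol treatment services". Secondary outcomes measures dependence with the two-item heaviness of smoking index and also counts cigarettes smoked, both at 6 weeks and 6 months.

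Data analysis sets the models. For dependence, "linear regression will be used to compare the heaviness of smoking index"; cigarettes smoked get negative binomial regression; both are compared between arms at each follow-up. Mixed models handle correlation within centres, and state or territory, service type and smoking policy are added as stratification factors. No other covariate is named. The one stated use of baseline characteristics is to present them by arm. The section also promises a full statistical analysis plan, which is not shown.

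Baseline characteristics includes in its list "income and source of income, education, postcode, smoking profile, and other dependencies (alcohol and other drug use". The heaviness index is not named there as a baseline item.

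For secondary outcomes, Sample size says that "the study will have 80 % power, with a 5 % significance level" to detect about a quarter of a standard deviation in nicotine dependence at 6 weeks, and about a third for continuous outcomes at 6 months.

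**The concern.** A client's own earlier smoking level is normally a strong predictor of the later level. If it stays out of the model, the variation it could explain remains in the residual and the interval for the intervention effect is wider than it needs to be. This matters more here because, on the protocol's own inputs, the quarter-SD target for dependence is already out of reach of an unadjusted comparison.

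Imbalance is the second issue. Allocation balanced services on service-level factors, not clients on dependence. The article describes randomisation as done and client recruitment as still to come, through centre staff, with the champion overseeing it in intervention centres. Clients can therefore enter after allocation through people who may know it. If the arms differ at baseline in measured smoking, part of that difference carries into an estimate that does not adjust for it.

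**Working it through.** **Inputs from Sample size.** "Assuming a 5 % significance level, 80 % power" (two-sided assumed, as sidedness is not stated); "providing a sample of 270 participants per experimental arm" at 6 weeks; "a design effect of 1.4 due to correlation of observations within treatment services"; a further 10% for unequal clusters, so 1.4 × 1.1 = 1.54. For 6 months, "We anticipate a 6-month attrition of 50" per cent of 450 leaves 225 per arm.

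**Assumptions not in the article.** The design effect quoted for abstinence also applies to the heaviness index. The correlation r between baseline and follow-up lies between 0.3 and 0.7. Adjustment scales the SD by √(1 − r²) and leaves the design effect unchanged. The stratification factors are given no credit for explained variance.

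**Formula.** Detectable difference in SD units = (1.960 + 0.842) × √(2 × DE / n) × √(1 − r²), where DE is the design effect and r = 0 means no baseline covariate.

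**The protocol's own figure, 6 weeks, n = 270, no baseline covariate.**
- DE 1.0: 0.241 SD; power for 0.25 SD is 83%.
- DE 1.4: 0.285 SD; power 69%.
- DE 1.54: 2.802 × √(2 × 1.54 / 270) = 0.299 SD; power 65%.

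The stated quarter SD comes back only if clustering is ignored, or nearly so with a one-sided 5% test at DE 1.4 (power 79%). Neither is stated. The 6-month figure does hold: with 225 per arm and DE 1.54 the detectable difference is 0.328 SD, with 81% power for a third of an SD.

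**With the baseline value as covariate, 6 weeks.**

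| r | Detectable, DE 1.4 | Detectable, DE 1.54 | Power for 0.25 SD (DE 1.4 / 1.54) | Equivalent sample, 1/(1 − r²) |
|---|---|---|---|---|
| none | 0.285 | 0.299 | 69% / 65% | 1.00 |
| 0.3 | 0.272 | 0.285 | 73% / 69% | 1.10 |
| 0.5 | 0.247 | 0.259 | 81% / 77% | 1.33 |
| 0.7 | 0.204 | 0.214 | 93% / 91% | 1.96 |

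**Correlation needed for 0.25 SD at 80% power.** √(1 − (0.25/0.285)²) ≈ 0.48 at DE 1.4; √(1 − (0.25/0.299)²) ≈ 0.55 at DE 1.54.

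**6 months, design effect recomputed for smaller clusters.** 450/33 = 13.64 clients per centre; 1 + 12.64 × 0.025 = 1.316; × 1.1 = 1.447. The detectable difference is 0.318 SD unadjusted and 0.303, 0.275 and 0.227 SD at r = 0.3, 0.5 and 0.7.

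**Imbalance.** The standard error of a chance baseline difference is √(2 × DE / 270) = 0.102 SD (DE 1.4) or 0.107 SD (DE 1.54), a 95% range of about ±0.20 to ±0.21 SD. With similar SDs at both times, a share r of it passes into an unadjusted estimate: at the edge of that range about 0.06 SD (r = 0.3), 0.10 (r = 0.5) or 0.14 to 0.15 (r = 0.7). This is the same precision loss seen within a single trial, not an addition to it.

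**The case against.** The strongest reply is that silence is not exclusion. A condensed article says its models include the stratification factors; it does not say that nothing else enters, and the promised analysis plan may add baseline terms. That stands: a reader might infer that the protocol rejects baseline adjustment, and nothing in it does. What remains is that the article does name adjustment terms and gives baseline data no role beyond presentation, so an analyst who follows it would fit the less precise model.

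A reader might also infer that the unadjusted comparison is biased, or that any imbalance enters the estimate in full. Neither is supported. Chance imbalance causes no bias on average, and only a share r carries through. Differential recruitment is possible under the described arrangements, but the article does not show that it occurs. If it did, adjustment would remove only the part explained by measured baseline smoking, not selection on unmeasured factors.

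The gain should not be oversold either. At r = 0.3 it is small (0.299 to 0.285 SD). Clients who quit smoke nothing whatever their baseline, which tends to lower r. A reader might infer that adjustment rescues the quarter-SD target; at r = 0.5 and DE 1.54 it still falls short, at 0.259 SD.

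Finally, the baseline heaviness index is not shown to exist: the article names only a smoking profile. That is a fair point, and the fix has to allow for it.

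**Conclusion.** The point holds as a matter of efficiency on two secondary outcomes. As specified, the 6-week comparison of nicotine dependence can detect about 0.30 SD rather than the stated quarter SD. Adding the baseline value would be worth between 1.10 and 1.96 times the sample over the assumed range of r, and would meet the stated target only if r is about 0.5 to 0.55 or more.

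The size rests on the assumed correlation, a two-sided test and the transfer of the abstinence design effect to the heaviness index. The SD figures apply to that index and are only indicative for the negative binomial model of cigarettes smoked. The analysis as written remains a valid comparison. The primary outcome is unaffected: everyone enters as a current smoker, so its own baseline value does not vary.

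**What to change.** In the analysis plan, and before follow-up data are seen by arm, pre-specify:

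- the baseline heaviness of smoking index as a covariate in its linear mixed model, at both follow-ups; if the baseline survey holds only one of the two items, adjust for that item;
- log baseline cigarettes per day as a covariate in the negative binomial mixed model for cigarettes smoked, at both follow-ups, with a stated rule for any baseline report of zero.

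First confirm that these items are in the baseline smoking profile. If they are, the cost is one covariate per model, with no extra clients, visits or measurements. Also restate the 6-week detectable difference for nicotine dependence with the clustering allowance and, if adjustment is assumed, the correlation it relies on.

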## Discussion

This will be the first methodologically rigorous trial to investigate the efficacy of an organisational change smoking cessation intervention within the drug and alcohol treatment setting. The main expected outcomes are improved health and a cost-effective sustainable organisational change intervention. Most smoking cessation interventions target the individual; this intervention targets the treatment environment and system to produce quality improvement in healthcare provision. Organisational change interventions hold great potential as cost-effective, sustainable strategies. A limitation of individual-targeted approaches is limited reach. Changes to systems reach larger numbers of people and changes are maintained long-term. They also address the environmental context in which the behaviour occurs. Given the study is a multi-state trial, the generalisability of the study outcomes to the treatment centres across Australia is increased. The intervention is also able to be modified for other health behaviour or clinical outcomes of interest (e.g. obesity, alcohol use).

The study is translational in nature with direct implications for health service provision in drug and alcohol treatment centres, including publicly run and non-governmentally run services. If cost-effective, the organisational change intervention has potential for building the capacity of addiction treatment centres to address their clients smoking in the longer term, as well as the potential transferability to other settings, reaching disadvantaged smokers in prisons and mental health settings and through social services. The intervention addresses existing inequity by targeting smoking cessation amongst people in drug and alcohol treatment centres – a cohort five times more likely than the general population to smoke tobacco.

## Trial status

The trial is ongoing.

## Abbreviations

ACT, Australian Capital Territory; ATTOC, Addressing Tobacco through Organizational Change; CO, carbon monoxide; HREC, Human Research Ethics Committee; NRT, nicotine replacement therapy; NSW, New South Wales; SA, South Australia; TNT, Tackling Nicotine Together.
